### Inclusion and Exclusion Criteria

Turkish participants living in Turkey are eligible if they are aged between 18 and 55 years, have internet access, have both a personal computer (PC) and a smartphone or tablet, and have mild to moderate depressive symptoms (Beck Depression Inventory-II [BDI-II] score between 10 and 29) [35]. Participants will be excluded if they have a BDI-II score above 29 or a medium-to-high suicidal risk (according to the Mini-International Neuropsychiatric Interview [MINI]), and they are advised to contact a psychiatrist or clinical psychologist by sending them an email [36,37].

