#### Primary Outcome: Depressive Symptoms

To measure depressive symptoms as the primary outcome, the Turkish version of the self-report BDI-II will be used at baseline, posttreatment, and follow-up [38]. It has 21 items in total describing depressive symptoms. Each item is scored on a 4-point scale, with a range of 0 (not at all) to 3 (severe). The total score ranges from 0 to 63. The BDI-II has good psychometric properties for online administration [39]. The Turkish version has been proven to have good reliability and validity [38,40]. The cut-off scores are 0 to 9 for minimal, 10 to 29 for moderate, and 30 to 63 for severe depression.

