### Sample Size

In this RCT, 2 experimental groups (receiving the intervention by either the internet or a mobile app) will be compared with a waiting list control group. The sample size is calculated based on an expected difference of Cohen *d*=0.45 (moderate) between 1 of the experimental groups and the control group as in previous studies [22,25]. “ *F* tests-analysis of variance repeated measures” will be applied in G-Power Statistical Power Analysis program version 3.1 and used for sample size calculation [55]. To obtain a power of .80 for a 1-tailed test and an alpha of .05, a total of 234 participants for 3 groups is needed. However, high attrition rates at posttest (25.0%) and at follow-up (30.0%) are expected based on previous studies [24,25]. Therefore, the sample size will be increased to 444 participants in total (allowing an attrition of 25.0%*30.0%=52.5%). This means that 148 participants are required at baseline for each group.

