### Statistical Analyses

The study will be reported in accordance with the consolidated standards of reporting trials guidelines [57]. The data obtained from the study will be evaluated and data tables created using the Statistical Package for Social Sciences version 25.0 statistical software program [58]. The significance level will be accepted as 95% CI (*P*<.05) in all statistical analyses. Quantitative (categorical) variables will be expressed as mean, SD, and upper and lower values in this study, whereas qualitative (continuous) variables will be expressed as numbers (n) and percentage (%). The Kolmogorov-Smirnov Test will be used to examine whether the quantitative data were distributed normally. To measure the efficacy of the treatment in this study, general linear model repeated measures analysis will be used to investigate the change on the primary outcome (BDI-II) scores in dependent variables for the total sample based on the intention-to-treat principle and for analyzing missing data [59]. McNemar tests will be used to measure categorical change as a version of the Chi-square test of independence in repeated measures of dependent groups. Furthermore, the Fisher exact Chi-square tests will be used if the number of crosstabs data is insufficient and the hypothesis is not achieved. Attrition will be defined as not completing any or 1 of the posttreatment measures. The notification effect will be analyzed by comparing the dropout rates of the Web and mobile versions. Finally, the correlation coefficient and statistical significance between the quantitative variables will be calculated by 2-way Pearson correlation analysis.

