### Clinically Significant Change

Analyses of clinically significant change on the primary outcome (BDI-II) will be conducted according to the Jacobson and Truax formula [60]. This method evaluates 2 criteria for each participant. The first is whether each participant’s BDI-II score has improved such that it is unlikely to be because of chance (Reliable Change Index [RCI]). The RCI is a function of a participant’s pretest and posttest scores, the SD of the population before treatment, and the test-retest reliability of the measure [55]. A participant is considered to have experienced reliable change if his or her RCI is greater than 1.96 [61]. The second criterion evaluated for participants shown to have reliable change is whether their posttreatment symptom level places them at a score of 10 or lower on the BI-II. A clinically significant change was determined if the participant had recovered and shown reliable improvement over time.

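### Categorical change is assigned to McNemar's test, a within-person pre-post test that makes no comparison with the wait-list

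*Protocol article*

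**What the plan says.** The Statistical Analyses section of the protocol article names one test for categorical change: "McNemar tests will be used to measure categorical change as a version of the Chi-square test of independence in repeated measures of dependent groups". It adds a conditional fallback, that "the Fisher exact Chi-square tests will be used if the number of crosstabs data is insufficient and the hypothesis is not achieved", and one threshold for everything: "The significance level will be accepted as 95% CI (*P*<.05) in all statistical analyses".

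Four other places bear on this.

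- Sample Size says that the two experimental groups "will be compared with a waiting list control group".
- Inclusion and Exclusion Criteria admits people who "have mild to moderate depressive symptoms (Beck Depression Inventory-II [BDI-II] score between 10 and 29".
- Primary Outcome: Depressive Symptoms sets the bands: "The cut-off scores are 0 to 9 for minimal, 10 to 29 for moderate, and 30 to 63 for severe depression".
- Clinically Significant Change uses a different recovery cut-off, a posttreatment level that "places them at a score of 10 or lower on the BI-II", and then defines the outcome: "A clinically significant change was determined if the participant had recovered and shown reliable improvement over time".

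The only categorical comparison between arms that the article describes is the dropout rate, Web against mobile.

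**The concern.** McNemar's test asks whether the proportion in a category differs between two occasions in the same people. It does not test independence, and arm does not enter it. Used as stated, it answers whether people changed, not whether they changed more than the wait-list did.

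The entry rule sharpens the problem. The admitted range, 10 to 29, is exactly the article's single moderate band, so nobody who enters on that score starts in the 0 to 9 band. Movement can go down into that band, but there is nobody in it to move out. The p-value then depends almost entirely on how many people improve. That count includes natural remission and regression to the mean after selection on the BDI-II, and the wait-list is in the trial to remove both.

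At stake is how a categorical result would be read. A significant pre-post shift in an active arm, reported at P<.05, could be taken as benefit when the wait-list shifted just as much.

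**Working it through.** **Plan's own figure.** The article states no figure for the McNemar analysis. The relevant sample size is 234 evaluable in three groups, or 78 per group. A two-group comparison of means with d = 0.45, two-sided alpha 0.05 and power 0.80 gives n = 2 × (1.960 + 0.842)² / 0.45² = 77.5, rounded up to 78 per group, and 3 × 78 = 234. So 78 is reproduced, although by a two-sided calculation and not the one-tailed test the article states; that does not affect this point. The other arm sizes used below are 148 (randomised) and 148 × 0.75 = 111 (after the expected 25% posttest loss). Applying both expected losses gives 148 × 0.75 × 0.70 = 77.7, again about 78.

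**Threshold with a zero opposite cell.** Let b be the number moving from 10 or more to 0–9, and c the number moving the other way. The exact two-sided p is 2 × P(X ≤ min(b, c)) with X ~ Binomial(b + c, 0.5). With c = 0 this is 2 × 0.5^b:

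- b = 5: 2 × 0.03125 = 0.0625
- b = 6: 2 × 0.015625 = 0.031

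The continuity-corrected chi-square, (|b − c| − 1)² / (b + c), also crosses .05 at six (5²/6 = 4.17, p = 0.041; for five, 4²/5 = 3.2, p = 0.074). The uncorrected version crosses at four (16/4 = 4.0, p = 0.0455). Six recoveries are 6/78 = 7.7%, 6/111 = 5.4% or 6/148 = 4.1% of an arm.

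**If the opposite cell is not quite zero.** With c = 1, b must reach 8: 2 × (1 + 9)/512 = 0.039. With c = 2, b must reach 10: 2 × (1 + 12 + 66)/4096 = 0.039.

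**Chance of a significant wait-list result.** This is P(at least 6 recoveries) from a binomial with c = 0. The recovery rates are assumptions, since the article gives none.

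| Assumed wait-list recovery | n = 78 | n = 111 | n = 148 |
|---|---|---|---|
| 5% | 20% | 48% | 75% |
| 10% | 80% | 97% | 99.8% |
| 20% | 99.9% | 100% | 100% |

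**The same data compared between arms.** With six recoveries in each of two arms, McNemar gives p = 0.031 in both, while Fisher's exact test between the arms gives p = 1.0 at 78, 111 or 148 per arm. Against six wait-list recoveries, an active arm needs 16 for Fisher p < .05 (15 by uncorrected chi-square) at any of these sizes.

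**The case against.** The strongest reply is that efficacy is assigned elsewhere. The article gives it to a repeated-measures general linear model of BDI-II scores under intention to treat, and nowhere says that a McNemar result will support an efficacy claim. This stands, and it limits the point to the categorical analysis. A reader might infer that the randomised control goes unused in the trial as a whole; the text does not support that.

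Second, the categorical variable is not named. The figure of six needs recovery to be 0 to 9 and the screening BDI-II to be the baseline value. Clinically Significant Change uses 10 or lower, so someone entering at exactly 10 already meets it and could move back out. Recruitment puts a BDI-II in the screening and Measures lists one at baseline, without saying whether they are one measurement. Both reservations stand. They move the threshold, to 8 or 10 with one or two reverse changes, but do not supply a comparison with control.

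Third, a reader might infer that categorical change would come out significant in every arm whether or not the intervention works. That is too strong: no wait-list recovery rate is given, and at an assumed 5% with 78 per arm the chance is only about 20%.

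Fourth, a reader might take McNemar to be the planned test for clinically significant change. That section does not assign it. Its silence on a between-arm test may simply be what a condensed article leaves to the full plan, so it is not counted here as a fault.

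The Fisher fallback does not answer the point: it applies only under a condition and is not described as a comparison between arms.

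**Conclusion.** The point holds in a limited form. The test named for categorical change is misdescribed and cannot separate the intervention from improvement that would have happened anyway. That part does not depend on how the categories are defined.

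The size does depend on assumptions. With recovery at 0 to 9, the screening score as baseline and a two-sided exact test, six recoveries are enough in any arm. How likely that is on the wait-list ranges from about 20% to 99.9% at 78 per arm, as assumed recovery goes from 5% to 20%.

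This should be corrected before analysis. It is a secondary analysis and does not threaten the primary result.

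**What to change.** Replace the McNemar sentence with a between-arm comparison of the categorical BDI-II outcome: each active arm against the wait-list, at posttest and at follow-up. Logistic regression adjusted for baseline BDI-II and age stratum, reported with the risk difference and its 95% CI, is one suitable form; a simpler between-arm test would also cure the defect. Analyse clinically significant change by the same comparison.

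Name the categorical variable, say whether the screening BDI-II is the baseline value, and reconcile the two cut-offs (0 to 9 in the outcome section, 10 or lower in Clinically Significant Change). If McNemar is kept, label it a within-arm description that carries no efficacy claim.

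The cost is one replaced sentence and a short clarification of definitions. No new data are needed.

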### Clinically Significant Change

Analyses of clinically significant change on the primary outcome (BDI-II) will be conducted according to the Jacobson and Truax formula [60]. This method evaluates 2 criteria for each participant. The first is whether each participant’s BDI-II score has improved such that it is unlikely to be because of chance (Reliable Change Index [RCI]). The RCI is a function of a participant’s pretest and posttest scores, the SD of the population before treatment, and the test-retest reliability of the measure [55]. A participant is considered to have experienced reliable change if his or her RCI is greater than 1.96 [61]. The second criterion evaluated for participants shown to have reliable change is whether their posttreatment symptom level places them at a score of 10 or lower on the BI-II. A clinically significant change was determined if the participant had recovered and shown reliable improvement over time.

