**Methods:**

Participants will be recruited through announcements in social media and the Middle East Technical University. Adults (18-55 years) with mild to moderate depressive symptoms (Beck Depression Inventory-II [BDI-II] score between 10-29) will be included in the study. Participants with a medium-to-high suicidal risk (according to the Mini-International Neuropsychiatric Interview) will be excluded. A 3-armed randomized controlled trial with a waiting control group will be utilized. A sample size of 444 participants will be randomized across 3 groups. The first experimental group will receive direct access to the Web version of the intervention; the second experimental group will receive direct access to the mobile app of the intervention as well as automated supportive short message service text messages based on PST. The control group consists of a wait-list and will gain access to the intervention 4 months after the baseline. The intervention is based on an existing PST for the Turkish population, *Her Şey Kontrol Altında* (HŞKA), consisting of 5 modules each with a duration of 1 week and is guided by a clinical psychologist. The primary outcome is change in depressive symptoms measured by the BDI-II. Secondary outcomes include symptoms of anxiety, stress, worry, self-efficacy, and quality of life. Furthermore, satisfaction with, usability and acceptability of the intervention are important features that will be evaluated. All outcomes will take place online through self-assessment at posttest (6-8 weeks after baseline) and at follow-up (4 months after baseline).

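### A post-treatment BDI-II of 10 counts as recovered, although the protocol's own bands and entry criterion treat 10 as symptomatic

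*Protocol article*

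**What the plan says.** Three parts of the protocol article bear on this point.

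- **Clinically Significant Change** applies two criteria. The first is reliable change: "A participant is considered to have experienced reliable change if his or her RCI is greater than 1.96". The second is checked only in those who pass the first, and asks whether the "posttreatment symptom level places them at a score of 10 or lower on the BI-II" (BI-II is plainly the BDI-II). Both are needed: "A clinically significant change was determined if the participant had recovered and shown reliable improvement over time".
- **Primary Outcome: Depressive Symptoms** gives the severity bands: "The cut-off scores are 0 to 9 for minimal, 10 to 29 for moderate, and 30 to 63 for severe depression".
- **Inclusion and Exclusion Criteria** admits people who "have mild to moderate depressive symptoms (Beck Depression Inventory-II [BDI-II] score between 10 and 29". The Methods part of the Abstract gives the same range.

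The section on clinically significant change gives no normative mean or SD and no other derivation of the 10.

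**The concern.** The word recovered should mean that a participant has left the symptomatic range. The only symptom ranges the article defines are its severity bands, and they place 10 just above the minimal range. The eligibility criterion agrees, because 10 is the lowest score that admits someone to the trial. A participant who improves reliably and finishes at exactly 10 would be reported as recovered while still inside the trial's own entry range.

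What is at stake is how the proportion with clinically significant change is read. Readers will take it as the share of participants who improved reliably and are no longer in the depressed range. Under the rule as written it also includes those who stopped on the boundary.

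**Working it through.** **Step 1. Compare the score sets.** Every input is stated in the article.

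| Set | Scores | Section |
|---|---|---|
| Recovered | 0 to 10 | Clinically Significant Change |
| Minimal | 0 to 9 | Primary Outcome |
| Eligible at entry | 10 to 29 | Inclusion and Exclusion Criteria; Abstract |

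Recovered and eligible overlap at one score, 10. Minimal and eligible do not overlap. Everyone at 9 or lower is also at 10 or lower, so the stated rule counts the same number as a limit of 9, or more, in every arm.

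**Step 2. What the reliable-change criterion filters out.** The required drop is 1.96 × SD × √(2 × (1 − r)). The article names the inputs, "the SD of the population before treatment, and the test-retest reliability of the measure", but gives no figures. I assume SD 5 to 8 and r 0.75 to 0.93.

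- Smallest: 1.96 × 5 × √(2 × 0.07) = 3.67, so someone ending at 10 must have entered at 14 or more.
- Largest: 1.96 × 8 × √(2 × 0.25) = 11.09, so someone ending at 10 must have entered at 22 or more.

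The excess is therefore confined to people who drop reliably and finish at exactly 10.

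**Step 3. Size within one arm (simulation, all values assumed).** Baseline is normal with mean 18, 20 or 23 and SD 6, truncated to 10 to 29. The mean drop is 2, 5 or 8, the SD of change 6 or 8, and r 0.75 or 0.93. The RCI uses the simulated baseline SD. Selected results for the share meeting both criteria:

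| Mean baseline | Mean drop | SD of change | r | Limit 10 | Limit 9 | Excess (points) |
|---|---|---|---|---|---|---|
| 23 | 2 | 6 | 0.75 | 9.0% | 7.5% | 1.4 |
| 20 | 2 | 8 | 0.93 | 20.5% | 18.1% | 2.5 |
| 20 | 5 | 8 | 0.93 | 31.1% | 27.9% | 3.2 |
| 18 | 8 | 6 | 0.93 | 48.4% | 43.9% | 4.5 |

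(The excess was computed before rounding.) Over all scenarios it is 1.4 to 4.5 points, or about 6% to 18% of those counted. A second model, with baseline uniform on 10 to 29, slope 0.7 and residual SD 7, gives a similar order: 12.7% against 11.4% (1.3 points) and 36.3% against 33.0% (3.3 points).

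**Step 4. Size for a between-arm difference.** The rule applies to all arms, so much of the excess cancels. Take the second and third rows above as control and treated arms:

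- limit 10: 31.1 − 20.5 = 10.6 points
- limit 9: 27.9 − 18.1 = 9.8 points
- change: about 0.8 points

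A 3-point contrast in mean drop is close to the planned effect: the Sample Size section assumes d = 0.45, and 3 / 0.45 gives an SD of 6.7, inside the assumed range. Subtracting the excesses for every such pair (drop 2 against 5, or 5 against 8) gives changes of 0.3 to 1.3 points. A 6-point contrast (2 against 8) gives 1.0 to 2.4. In the second model, one pair of arms moves from a difference of 17.2 to 16.1 points, a change of 1.1.

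**The case against.** The best defence is that a Jacobson-Truax cut-off need not coincide with a severity band. It can be derived from normative and clinical distributions and may fall inside the symptomatic range. That is fair, and it is why the fix leaves room for a justified 10. But the article offers no such derivation, and 10 sits exactly on the edge of its own bands, where writing 10 or lower in place of below 10 is an easy slip. The text does not show which it is.

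It can also be said that little depends on this. That largely stands. Clinically significant change is not among the outcomes named in the Abstract, and the Limitations section already says that the trial cannot speak to recovery from a depressive disorder.

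A reader might infer more than the article supports:

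- *Someone who enters at 10 and does not change counts as recovered.* No. The second criterion is applied only after reliable change has been shown.
- *A reliably worsened participant could qualify, because the RCI has no stated direction.* No. The section speaks of improvement, and anyone who enters at 10 or more and ends at 10 or less cannot have worsened.
- *The reliable-change threshold is too lenient because the SD of a sample truncated to 10 to 29 is paired with a reliability from an unrestricted sample.* The article names the source of neither quantity. The mismatch would be the reader's own assumption, and an article commonly leaves such detail to the full plan.

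**Conclusion.** The inconsistency is real and can be seen from the text alone: a score of 10 is symptomatic at entry and in the bands, yet recovered after treatment. The direction is certain within each arm, since the proportion can only equal or exceed the one at 9 or lower.

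The size is modest and conditional. It is roughly 1 to 4.5 percentage points per arm under the assumed baselines, changes and reliabilities, and about 1 point on a between-arm difference when the treatment effect is near the planned one. The article fixes neither figure. It also does not fix the direction of the between-arm effect, which depends on how many in each arm end at exactly 10.

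It would be wrong to conclude that the trial's main result is inflated. The primary comparison uses BDI-II scores, not this cut-off. This is a one-point boundary error in a supporting analysis, worth correcting before the data are analysed.

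**What to change.** Reconcile the three sections by setting the second criterion in Clinically Significant Change to a BDI-II of 9 or lower, which is the protocol's minimal band. The eligibility range need not change.

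If 10 was chosen on purpose as a Jacobson-Truax cut-off, state which form of the cut-off was used and the means and SDs behind it, and report the proportion at 9 or lower beside it.

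The cost is one number, or one or two sentences and an extra line in a results table. Recruitment, sample size and data collection are not affected. The drawback is a slightly lower reported proportion with clinically significant change.

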### Per-Protocol Analysis

Secondary per-protocol analyses will be performed for participants who completed all the measurements and all 5 modules of the intervention (if randomized to the experimental conditions).

## Results

A total of 444 participants with mild to moderate depressive symptoms will be recruited from March 2018 to February 2019 or until the recruitment is complete. We expect the final trial results to be available by the end of May 2019. This trial is funded by the Scientific and Technological Research Council of Turkey under its National Postdoctoral Research Fellowship Programme 2016/1.

## Discussion

### Strengths

In an earlier report, RUSIHAK raised alarm concerning mental health care in Turkey [1]. A new mind-set and alternative solutions for this challenging problem are needed. E-mental health could be an inventive solution to reach, treat, and monitor people with psychological problems. The flexibility in time and place and the high levels of anonymity and accessibility could make a positive difference to mental health care.

To our knowledge, this project will be the first trial studying the effects of guided PST in a Web-based and mobile app for depressive symptoms in the general population in Turkey. In addition, the effects of receiving notifications based on PST techniques in the app will be evaluated. Although notifications seem to be a promising solution to increase adherence, the impact of it has earlier been evaluated as disruptive [62]. As Turkey has some major shortcomings in providing mental health care, HŞKA can bridge this gap in several ways, such as providing alternative and evidence-based care besides pharmacotherapy and relatively easily accessible health care for a wider population in need of help. Online guided self-help can be an innovative way to reach and treat populations with limited access to mental health care. The first and second phases of the study will shed light on the general stance of the Turkish population toward mental health and the usability and acceptability of the apps.

